**Intervention study design**

The study will be a **cluster randomized intervention trial,** with **cross-over design** carried out in three phases:

(1) a 3 month screening reinforcement phase during which the adherence to the admission and discharge MRSA screening protocols will be promoted and monitored monthly to achieve > 80 % compliance rate, application of isolation precautions to MRSA colonized patients will be measured and checked to achieve > 80 % compliance and the MRSA acquisition rate will be checked to lie within 95 % confidence limits of the projected 3% estimate. In addition, the length of stay per ward will be measured and checked for homogeneous distributions.

(2) a 5 month conventional detection test (standard care) phase during which MRSA screening will be performed by optimized conventional culture methods 6 days a week during working hours.

(3) a 5 month rapid detection test intervention phase during which admission MRSA screening will be performed by rapid PCR testing 7 days a week during working hours.

After eligible wards in each hospital have been checked to meet these inclusion criteria in phase (1), the sequential order of inclusion of eligible study wards in phase (2) and (3) will be randomly assigned within each centre by assigning a number to each ward and using a computer generated list of random numbers per study arm in each hospital so that one half of the wards will start phase (2) for the first 5 months and then phase (3) for the following 5 months whereas the other study wards will be “crossed-over” to follow the reverse sequence. No wash-out period will be used between phase (2) and (3). If the analysis of patient length of stay by ward indicates homogeneous distribution with markedly different median values between wards, stratified randomisation of wards within short/long (below/above pooled median) stay groups will be considered.

The planned study start date is: November 3rd, 2008 for the baseline observation and completion is planned on December 31st, 2009 (post-poned to end January, 2010 see addendum).

Admission screening: evaluation of patient sampling procedures:

During the entire study period (baseline and intervention phase), the infection control nurse responsible for the study will perform daily rounds in each of the study wards to ensure that screening of all newly admitted patients is being done systematically and without delay.

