The **primary analysis** will be based on Poisson regression two level model (individual patient and unit exposure) performed at each hospital level to assess the impact of the intervention on local incidence-density of MRSA nosocomial colonisation, and ajusted for four potentially confounding factors. The dependent variable will be endpoint 1 above. The ward level **independent variables** will include (1) **intervention arm**, (2) MRSA **colonisation pressure** (as determined by monthly proportion of MRSA colonisation-days/total patient-days among patients admitted during the preceding month in one particular ward), (3) **staff** **compliance with standard and isolation precautions** (as determined by a sample of 50 observations per ward/ trial period, including 25 care opportunities for patients under MRSA isolation precautions and 25 for patients cared for with standard precautions; see appendix 6 for precautions compliance monitoring procedure) (4) **antibiotic use** (as determined by cumulated number of Defined Daily Doses of J01 ATC class of antimicrobial drugs per monthly period) and (5) monthly bed occupancy rate.

Heterogeneity of effect by ward/hospital will be assessed. **To quantify the protective efficacy of the intervention** for the at risk population per centre, the adjusted Rate Ratio (and 95% confidence interval) of nosocomial MRSA acquisition will be calculated for the intervention arm in all study wards per hospital. Pooled analysis of average effect for both hospitals will be calculated. In case of significant heterogeneity between hospitals, hospital level will be added as covariate in the model.

**Secondary analyses** will include:

A. Logistic regression two level models (individual patient and unit exposure) will be performed at each hospital level to assess the impact of the intervention on local cumulated incidence of MRSA nosocomial colonisation. The dependent variable will be endpoint 6 above. The **independent variables** will include patient age, sex and the 5 independent ward level indicators as described above for the primary Poisson analysis.

Heterogeneity of effect by ward/hospital will be assessed. Pooled analysis of average effect for both hospitals will be calculated. In case of significant heterogeneity between hospitals, hospital level will be added as covariate in the model.

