# Two-Center Intervention Study to Evaluate the Impact of Rapid Molecular Screening on Nosocomial Transmission of Methicillin-Resistant *Staphylococcus aureus* (MRSA).

# Addendum 1 to the protocol – modification of analysis plan (February 7th, 2009)

Based on the results of the base-line period (November 3rd, 2008 –January 15th, 2009), 7 wards of Erasme hospital and 6 wards of AZ St Jan hospital have been randomized and allocated either to the intervention or control arm for the first 5 month study period to begin on February 9th, 2009. Stratified randomization of wards was performed according to the hospital and average patients’ length of hospital stay.

In the base-line period, the compliance rates with key processes of care were achieved (admission screening cultures and infection control precautions > 80%) or closely approached (discharge screening cultures 68% and improving during the baseline weeks). However, the incidence of MRSA nosocomial acquisition was lower than hypothesized in the protocol: 0.79% (95%CI: 0.34% - 1.55%). This incidence rate was unexpectedly low compared to previously recorded rates. When considering the higher limit of the 95%CI, the planned sample size allows detection of a 50% reduction in incidence of nosocomial acquisition with 80% power and taking into account a potential cluster effect only if the pooled incidence in both hospitals combined is analysed as the primary endpoint. Therefore, although heterogeneity between the two hospitals will be studied as planned, the pooled results for both hospitals will be presented and analysed as the primary endpoint.

An additional interim analysis is planned three months after the beginning of the study to obtain a new estimate of the incidence of MRSA nosocomial acquisition in the control units and to check if the number of subjects is large enough to reach the objectives.

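### The pooled primary model adds hospital only after a weak heterogeneity test, answers effect heterogeneity with a main effect, and does not list the length-of-stay stratum

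*Protocol*

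**What the plan says.** The Intervention study design section says that the order of phases "will be randomly assigned within each centre", and that "stratified randomisation of wards within short/long (below/above pooled median) stay groups will be considered". Addendum 1 confirms what was done: "Stratified randomization of wards was performed according to the hospital and average patients’ length of hospital stay". It also gives the number of clusters: "7 wards of Erasme hospital and 6 wards of AZ St Jan hospital have been randomized".

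The primary analysis paragraph (Study endpoints and statistical analysis) specifies a "Poisson regression two level model (individual patient and unit exposure) performed at each hospital level". It lists five ward-level variables: intervention arm, colonisation pressure, staff compliance, antibiotic use and bed occupancy. Neither hospital nor stay stratum is listed. The paragraph then plans an assessment of whether the effect varies by ward or hospital, an adjusted RR with 95% confidence interval for each hospital, and a pooled average effect. Its rule for the model is "In case of significant heterogeneity between hospitals, hospital level will be added as covariate in the model". Secondary analysis A repeats the rule for the logistic model.

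Addendum 1 changes which result is primary: "the pooled results for both hospitals will be presented and analysed as the primary endpoint". It keeps the study of heterogeneity as planned and does not revise the rule.

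**The concern.** While the primary model was fitted separately in each hospital, hospital was conditioned on automatically and the rule affected only a supporting pooled estimate. Once the pooled result became primary, the same rule came to decide the form of the primary model. Three things are then unsatisfactory.

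- A factor used to stratify the randomisation enters the model only if a data-dependent test is significant. The usual principle is to analyse by the strata used, whatever any test shows.
- The second stratification factor, length of stay, is not in the listed model.
- The trigger and the response do not match. What is assessed is a difference in intervention effect between hospitals. What is added is a covariate, in ordinary usage a main effect. It lets baseline acquisition rates differ but leaves the arm effect common to both hospitals.

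At stake is whether the primary model is fixed in advance and whether a difference in effect between two quite different hospitals is modelled as such.

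**Working it through.** The plan gives no figure for the heterogeneity test, so there is none to reproduce.

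**1. Power of the trigger.** Inputs: 1,850 patients per arm in each hospital (Sample size estimate), hence 3,700 control patients; baseline acquisition 0.79% with upper 95% limit 1.55% (Addendum 1). The contrast of RR 0.5 in one hospital and 1.0 in the other, equal exposure in all four cells, and a two-sided 5% test are assumptions.

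Control cases: 3,700 × 0.0079 ≈ 29 and 3,700 × 0.0155 ≈ 57, so c ≈ 14.5 or 28.5 per hospital.

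SE of the difference in log RR = √(1/c + 1/(0.5c) + 1/c + 1/c) = √(5/c). The true difference is ln 2 = 0.693.

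| Control rate | c | SE | z = 0.693/SE | Power |
|---|---|---|---|---|
| 0.79% | 14.5 | 0.587 | 1.18 | 22% |
| 1.55% | 28.5 | 0.419 | 1.65 | 38% |

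With this degree of real heterogeneity, hospital would stay out of the model in about 62% to 78% of trials. Clustering is ignored; variation between periods within a ward would lower the power further.

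**2. What the response does.** A 13-ward, two-period crossover was simulated with Poisson counts (1,500 runs per setting). Inputs the documents do not give are assumed: a control rate centred on 1.55%, a threefold rate difference between hospitals, a twofold difference between stay strata, ward log-SD 0.3, and ward-period size varying by 10% or 25% (CV). With true RRs of 0.35 and 0.9 in the two hospitals, the pooled estimate was 0.74 both without and with a hospital main effect. It lies nearer 0.9 because that hospital had the higher assumed rate. The main effect leaves the heterogeneity where it was. The test detected this wider contrast in about 49% of runs at 1.55% and 21% at 0.79% (CV 10%).

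**3. What omitting the strata costs.** With a common RR of 0.5, the same simulation gave an estimate of 0.50 and power of 92% to 93% with no strata, hospital, hospital plus stay, or ward effects. With no effect, rejection at a nominal 5% was:

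| Model | CV 10% | CV 25% |
|---|---|---|
| No ward term, no strata | 4.9% | 7.3% |
| No ward term, hospital + stay | 4.4% | 5.3% |
| Ward random intercept, no strata | 6.5% | 5.2% |
| Ward random intercept, hospital + stay | 6.2% | 5.0% |

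The last two rows use 400 runs per setting, so the Monte Carlo standard error is about √(0.05 × 0.95/400) = 1.1 percentage points; for 1,500 runs it is 0.6. With the ward intercept and RR 0.5, power was 86.2% without strata and 86.0% with them at CV 10%, and 87.2% for both at CV 25%. The excess at 7.3% is absent once the model has a ward level, as the protocol's two-level model does if its unit level is a ward effect.

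**4. Expected events.** With RR 0.5 the intervention arm has half the control cases: 29 × 1.5 ≈ 44 in total, or 57 × 1.5 ≈ 86.

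**The case against.** The strongest reply is that the crossover makes the omission nearly harmless. Every ward receives both arms, and only the order is randomised. Hospital and stay stratum are ward attributes, so they occur in both arms and a ward effect absorbs them. This stands, and step 3 supports it. A reader might infer that the primary estimate is biased or that its type I error is materially inflated; neither the design nor these checks support that.

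Second, a reader might infer that a difference between hospitals would be hidden behind one average RR. That is not so. The primary analysis paragraph plans an adjusted RR with 95% confidence interval per hospital without any condition, and Addendum 1 keeps the study of heterogeneity. Only the model's response to heterogeneity is mis-specified.

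Third, absence of the stay stratum from a list is not a decision to exclude it. Stratifying by stay was still only a possibility when the list was written, and a statistical analysis plan may supply the term. That weakens this part of the point. It does not touch the hospital rule, which the protocol states outright.

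Fourth, an interaction test would be as weak as the existing test. That is true, and it is why the interaction should be reported as an estimate with its interval and not used to choose a model.

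Finally, the heterogeneity in the rule could be read as a difference in baseline rates, for which a main effect would be apt. The same paragraph, however, speaks of heterogeneity of effect, and even on this reading a stratification factor would depend on a test.

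**Conclusion.** The point holds as a flaw in a stated rule with small numerical consequences. Since Addendum 1, the form of the primary pooled model depends on a test with about 22% to 38% power for RR 0.5 versus 1.0. The response to a positive test cannot represent a differing effect, and the stay stratum used in randomisation is not among the listed variables. Under the two-level model, adding the strata barely changes the estimate, power or type I error.

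The power figures assume equal exposure, equal control rates in the hospitals and no clustering. The simulations rest on assumed variation between hospitals, strata and wards, with no extra variation between periods within a ward. The correction is worth making because it fixes the primary model in advance at almost no cost. It gives no reason to doubt the trial's pooled conclusion.

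**What to change.** In the primary analysis paragraph, and likewise in secondary analysis A, state that the pooled Poisson and logistic models include hospital and the length-of-stay stratum used in randomisation as fixed terms, regardless of any test.

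Replace the conditional sentence by a pre-specified arm-by-hospital interaction, fitted as a separate heterogeneity analysis. Report the ratio of the hospital RRs with its 95% confidence interval, whatever its p-value, beside the hospital-specific RRs already planned. Say plainly that its power is low and that a non-significant result does not show equal effects.

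This takes a few sentences and uses factors already recorded for randomisation. The downside is two extra ward-level parameters (taking the stay stratum as short/long) on top of the five listed variables, with 13 wards and about 44 to 86 expected cases. Keeping the interaction out of the primary model limits that burden.

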In addition, during a defined period, he or she will collect individual patient data on a subset of 20 % of included patients to identify risk factors for MRSA carriage based on history taking (notion of previously recorded MRSA carriage, transfer from other department or hospital, transfer from a nursing home, hospital stay in the previous year, attending outpatient care at a clinic in the previous year, presence of chronic skin sores, or living/working in a livestock farm, working as veterinarian or in a slaughterhouse). These data will be analysed to estimate the predictive value of these risk factors for the carriage of MRSA.

In the control arm, as per routine infection control policy in each institution, all patients admitted to study wards and presenting with will be sampled within 24 h after admission by taking swabs of anterior nares, throat, perineum and of any wounds, bladder catheter or intravenous catheter exit site (see appendix 1 for conventional MRSA screening procedures). Patients with previously recorded active MRSA carriage will be presumptively placed in contact isolation until three new series of conventional selective cultures of relevant body sites are found negative.

In the rapid test intervention arm, all patients admitted to study wards will be sampled within 24 h after admission. To ensure comparison of like with like, sample taking will include: (1) a swab from the anterior nares for PCR testing according to the test manufacturer’s instructions (see appendix 2 for rapid PCR screening test procedure); (2) the swab of anterior nares, and swabs from throat, perineum and of any wounds, bladder catheter or intravenous catheter exit site will be processed by conventional testing (see appendix 1 for conventional MRSA screening procedures). Patients with previously recorded active MRSA carriage will not be sampled for PCR testing but placed in pre-emptive isolation until three series of conventional selective cultures of relevant body sites are found negative.

Thus, patients in each arm will be managed identically, except that the rapid PCR test will be performed and its results made immediately available to infection control and clinical staff in the intervention arm.

MRSA isolates will be tested for mupirocin susceptibility and stored at -80°C for genotyping.

Additional contact isolation precautions.

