MRSA contact isolation precautions will be applied to hospitalised patients as per local policy (see appendix 3 for isolation procedures in HE and AZSJ hospitals) either when previously recorded in the laboratory information file as active MRSA carrier or as soon as newly detected by either culture or PCR. Patients will be released from isolation after three consecutive culture screens for MRSA are negative after the end of therapy. Topical decolonisation therapy will be applied as per routine protocol in each institution (see appendix 4 for decolonisation procedures in HE and AZSJ hospitals) to all patients with either a positive MRSA culture and/or PCR.

Notification of screening results and process time recording.

Results of MRSA screening tests will be notified electronically to clinicians by either the technologist or biologist on duty through the laboratory information system (LIS) as well as with a telephone call to the Infection Control study nurse (during working hours) or the unit head nurse (outwith working hours). For culture tests, both presumptive positive results based on colony pigmentation typical for MRSA on chromogenic selective culture medium as well confirmed identification results will be notified immediately by the same communication modes. The precise timing (date, hour, min) of all telephonic result notifications will be recorded in the LIS.

The date and time (hour; min) of patient admission to study ward, as well as of patient placement in contact isolation or release from isolation will be recorded by the infection control study nurse. The date and time (hour; min) of screening sample reception in the laboratory, as well as of result electronic notification will be recorded by the LIS.

Primary outcome monitoring and case finding procedures.

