**Secondary endpoints**

These will include three related process of care indicators:

1. Time (h) between admission and notification of MRSA positive culture/PCR
2. Time (h) between admission and placement of newly detected MRSA carrier in contact isolation

Secondary endpoints will also include the following microbiologically-documented outcomes:

1. Number of patient-days of MRSA positive patients cared for with standard precautions and not isolated
2. Cumulative incidence of MRSA nosocomial colonisation, defined as number of new cases of hospital-acquired MRSA (first positive culture >48 h after admission) divided by the number of admitted patients who stayed ≥ 3 days and were MRSA negative on admission by culture and PCR testing, if performed.
3. Cumulative incidence of MRSA nosocomial infection, defined as number of new cases of hospital acquired MRSA infection (according to CDC definitions for nosocomial infection and with first MRSA positive culture > 48 h after admission) divided by number of admitted patients who stayed ≥ 3 days.
4. Number of clusters of ≥ 2 cases/unit of acquired MRSA colonisation with a clonally related strain, defined as a MRSA strain with the same spa type or PFGE major type.
5. Sensitivity and specificity of rapid PCR test compared to conventional culture for MRSA screening, taking into account one parallel set of admission nasal screening samples per patient.

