C. The median process time intervals (endpoints 2-4 above) and number of missed isolation days (endpoint 5 above) will be compared by Wilcoxon tests for patients within the same unit/hospital between arms; median times (interquartile range) will be compared for each study phase and hospital.

D. In addition, monthly rates of endpoints 1, 6 and 7 will be plotted over time and interrupted time-series, segmented linear regression analysis of temporal trends per study periods will be performed for each hospital. The hypothesis to be tested is that there will be a significant drop in the level of rates from the beginning of the intervention compared to the baseline or control period, possibly associated with a negative change of slope due to a decreasing trend in the intervention period.

E. Diagnostic accuracy (clinical sensitivity and specificity) will be calculated for the rapid PCR test (MRSA GeneXpert, Cepheid) compared to conventional culture as gold standard based on all matched nasal swabs (N=3,700) tested in parallel during the 10 month trial period.

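### Process times are compared on case sets that PCR-only positives enter in one arm only, with a patient-level Wilcoxon test that leaves ward-by-period correlation out

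*Protocol*

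**What the plan says.** All references are to the protocol.

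- **Test.** Secondary analysis C, under the study endpoints and statistical analysis, takes the process time intervals and the missed isolation days and says they "will be compared by Wilcoxon tests for patients within the same unit/hospital between arms". Medians and interquartile ranges are also to be given by phase and hospital.
- **Randomisation.** Under Intervention study design, "the sequential order of inclusion of eligible study wards in phase (2) and (3) will be randomly assigned within each centre". Addendum 1 reports that "7 wards of Erasme hospital and 6 wards of AZ St Jan hospital have been randomized", 13 clusters in all. The primary analysis and secondary analysis A both use two-level models.
- **Endpoints.** The process endpoints are "Time (h) between admission and notification of MRSA positive culture/PCR" and "Time (h) between admission and placement of newly detected MRSA carrier in contact isolation". A third outcome counts unisolated patient-days of MRSA-positive patients without saying positive by which test.
- **Detection.** Isolation starts for known carriers, or "as soon as newly detected by either culture or PCR".
- **Difference between arms.** Both arms take the same cultures. The stated difference is that "the rapid PCR test will be performed and its results made immediately available to infection control and clinical staff in the intervention arm". Known carriers are not PCR-tested.

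No text limits the process endpoints to culture-positive carriers.

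**The concern.** Two features of analysis C are fixed in the protocol and work against a clean comparison.

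First, the unit. Carriers in one ward and period share staff, laboratory workload and access to single rooms, which Appendix 3 makes subject to availability. Within a ward, arm coincides with calendar period, so a ward-by-period shift cannot be told apart from an arm effect by comparing patients inside that ward. A patient-level rank test counts such carriers as independent.

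Second, the case set. A patient who is PCR-positive and culture-negative at admission becomes a case in the PCR arm, with a time set by the fast test. The same patient in the control arm is never a case. This holds whether the PCR result is a false positive or true carriage that culture missed. The medians then compare different kinds of patients, and no choice of test repairs that.

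These outcomes are the direct evidence for the causal step behind the sample-size hypothesis, namely that earlier detection lowers acquisition. Baseline acquisition was only 0.79% (Addendum 1), so the process results may carry much of the interpretation.

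**Working it through.** **Plan's own figure.** The protocol gives no figure for analysis C. The nearest is the allowance in the sample size estimate for clustering and time dependence: 1,237 × 1.5 = 1,855.5, given as 1,850 per arm per hospital. It reproduces to rounding.

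**(a) Clustering, with the protocol's factor.** If the variance is understated by a design effect DE, a nominal two-sided 5% test has type I error 2 × [1 − Φ(1.96/√DE)]. With DE = 1.5, 1.96/1.2247 = 1.600, giving 11.0%. The factor is borrowed: it was set for the acquisition endpoint.

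**(b) Clustering, by simulation under no effect.** There are 13 wards in a two-period cross-over, with 1,000 runs per setting. Total variance is 1 and stable ward variance 0.10. The ward-period ICC is assumed, because the documents give none. Carriers per ward-period follow from 2 × 1,850 = 3,700 patients per arm over 13 wards, about 285 each. At assumed carriage of 2%, 5% and 10% that is about 6, 14 and 28. Rejection rates at nominal 5%:

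| Carriers per ward-period | ICC | Pooled Wilcoxon | Ward-stratified Wilcoxon | t-test on within-ward differences |
|---|---|---|---|---|
| 6 | 0 | 5.1% | 5.4% | 7.3% |
| 6 | 0.02 | 5.2% | 5.2% | 5.1% |
| 6 | 0.05 | 7.4% | 8.5% | 6.0% |
| 6 | 0.10 | 11.3% | 12.1% | 5.5% |
| 14 | 0 | 3.4% | 4.4% | 5.0% |
| 14 | 0.02 | 6.3% | 8.2% | 5.5% |
| 14 | 0.05 | 13.3% | 15.7% | 6.1% |
| 14 | 0.10 | 19.2% | 21.4% | 6.1% |
| 28 | 0 | 3.4% | 4.3% | 3.3% |
| 28 | 0.02 | 10.0% | 11.4% | 4.8% |
| 28 | 0.05 | 19.1% | 21.1% | 4.8% |
| 28 | 0.10 | 30.0% | 33.4% | 5.9% |

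Seven wards, as in one hospital, give similar rates. Stratifying by ward does not help, because the correlation that matters lies between periods within a ward.

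**(c) Case sets.** Per hospital, with n = 1,850 in the PCR arm, carriage p and specificity s taken against culture:

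- PCR-only positives = 1,850 × (1 − p) × (1 − s)
- culture-positive carriers = 1,850 × p
- PCR-only share = PCR-only / (PCR-only + culture-positive)

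The 97% specificity is the preliminary figure in the Introduction. The 99% and the carriage values are assumptions.

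| Carriage p | Culture-positive | PCR-only, s = 97% | Share | PCR-only, s = 99% | Share |
|---|---|---|---|---|---|
| 2% | 37.0 | 54.4 | 60% | 18.1 | 33% |
| 5% | 92.5 | 52.7 | 36% | 17.6 | 16% |
| 10% | 185.0 | 50.0 | 21% | 16.7 | 8% |

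The control arm has none. The counts treat every culture-negative admission as PCR-tested, so they are approximate.

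**(d) What this does to the median.** For illustration, let culture-positive carriers have the same times in both arms (assumed median 60 h) and PCR-only patients a median of 20 h (assumed). At 97% specificity the PCR-arm median falls from 60 h to about 31, 45 and 53 h at 2%, 5% and 10% carriage. The Wilcoxon test rejects in 95-100% of runs, with no speed-up for any culture-positive carrier.

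**The case against.** **Ward is not ignored.** A reader might infer that analysis C disregards the ward randomisation altogether. The wording does not support that. It compares patients within the same unit or hospital, and on its natural reading it conditions on ward, although the slash leaves this open. What remains is ward-by-period correlation, whose size the documents do not give.

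**The null is hardly plausible.** The protocol expects unisolated stay to fall from 3 days to 0, so an inflated type I error is unlikely to change the conclusion that PCR is faster. This stands. Clustering mainly affects the stated precision.

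**All detected patients are a fair set.** PCR-only patients are isolated under trial policy, so time to isolation among everyone detected is a legitimate measure of the strategy. Analysis E will also show how many nasal samples are PCR-positive and culture-negative. Both are true, but neither makes the medians a comparison of the same carriers. The direction also differs by outcome: extra PCR-only patients shorten the time medians, yet add days to any arm total of missed isolation days.

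**Early discharge.** A reader might infer that carriers discharged before a result or before isolation are lost, mostly in the slower arm. The documents do not say so. Notification times are logged by the laboratory system whether or not the patient is still present, and unisolated days include carriers who were never isolated. If slow control carriers did lose their isolation time, the control median would shorten and the PCR advantage would be understated. How such cases are handled may properly sit in a statistical analysis plan.

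**Conclusion.** The point holds in two parts of unequal weight.

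The case-set difference is the main one, because it can bias the medians themselves. Its existence follows from the endpoint definitions and from PCR being run in one arm. Its size, about 8-60% of the PCR-arm set, rests on assumed carriage of 2-10% and on specificity between the preliminary 97% and an assumed 99%. It would be wrong to conclude that the expected PCR advantage is an artefact. The documents support only that part of it could come from patients with no counterpart in the control arm.

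The clustering part is lesser. P-values may be too small, by an amount that depends on an unknown ward-period ICC: none at zero, and up to about 30% type I error (33% if stratified by ward) at an ICC of 0.10 with 28 carriers per ward-period. The two-level models used for the primary analysis and analysis A show that the protocol accepts non-independence elsewhere.

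These are secondary endpoints. The change should be made, but the primary analysis is not affected.

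**What to change.** 1. Define the case set for the process endpoints and the missed isolation days identically in both arms: carriers positive on admission culture and not previously known. Each keeps the time at which first notified or isolated, by whichever test. Culture is run in both arms, so no new data are needed.
2. Report PCR-only positives separately, and give results for all detected patients as a supplementary, strategy-level comparison.
3. Replace the patient-level Wilcoxon test with an analysis that respects the ward cross-over. Either pool within-ward differences over the 13 wards, stratified by hospital, or fit a model with ward and ward-period effects and a period term. Pooling agrees with Addendum 1, which already pools the hospitals for the primary endpoint.
4. Give hospital-specific medians and interquartile ranges descriptively.

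The cost is a change of wording, with wider intervals. A ward-level test within one hospital would have little power. With 6 pairs, a signed-rank test reaches two-sided p < 0.05 only if all six wards agree (2/64 = 0.031; the next value is 4/64 = 0.0625), and 7 pairs are little better. Ward medians from about 6 carriers would also be unstable, which favours the model if carriage is low.
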